| Background and rationale | 6a | Description of research question:  Ozone therapy may offer clinical benefit as an adjuvant treatment of Chemotherapy-induced peripheral neuropathy  Participants will be randomized (1:1) to Ozone or Control (placebo) groups. All will continue standard care and undergo 40 rectal insufflation sessions over 16 weeks (3×/week for 8 weeks, then 2×/week). The Ozone group receives O₃/O₂ (10–30 µg/mL); the Control group receives O₂ (0 µg/mL). Volumes range from 180 to 300 mL as tolerated. |
|  | 6b | Explanation for choice of comparators: Oxygen is the vehicle of ozone |
| Objectives | 7 | The **primary objectives** are to evaluate the effect of adding ozone on change from baseline at week 28 (end of follow-up) in: i) patients' self-perceived level of paraesthesia (numbness and/or tingling), and ii) patients' self-perceived health-related quality of life (HRQoL).  **Secondary objectives** include evaluating the effect of ozone on: i) additional direct costs, ii) evolution of neuropathy symptoms (CTCAE v5.0, QLQ-CIPN20), iii) evolution of quality of life (EQ-5D-5L, and QLQ-C30), iv) evolution of anxiety and depression, v) evolution of biochemical parameters related to oxidative stress and chronic inflammation, vi) evolution of infrared images and spectral signatures in hyperspectral images obtained from hands and feet, and vii) toxicity of rectal ozone treatment. Except for direct costs and toxicity, all variables will be assessed at week 16 (end of insufflations) and week 28 (end of follow-up). Masking will be triple: participant, care provider, and outcomes assessor. |
| Trial design | 8 | OzoParQT is a Phase II–III randomized, triple-blind trial including 42 adults (≥18 years) with any cancer and Grade ≥2 CIPN lasting ≥3 months. Eligible patients must be off neurotoxic chemotherapy for ≥3 months, with stable/remitted disease and ≥6-month life expectancy. |
| Methods: Participants, interventions, and outcomes | | |
| Study setting | 9 | Academic hospital.  Hospital Universitario de Gran Canaria [name], 35019 Las Palmas de Gran Canaria, Spain. |

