| Sequence generation | 16a | A stratified randomization will be carried out based on sex to ensure a homogeneous distribution between the two arms. Randomization will be managed by a statistician, who will be independent of those who analyse the results. Opaque, sealed envelopes containing the assigned treatment group (coded as Group A or Group B) will be used. The principal investigator will maintain a record of patient names, randomization dates, and code numbers. However, the key linking the code to the actual treatment (ozone or oxygen) will be known only to the randomization investigators and Chronic Pain Unit staff, remaining hidden until the analysis is completed. This ensures triple blinding of participants, care providers (oncologists/haematologists), and outcomes assessors. |
| Allocation concealment mechanism | 16b | Mechanism of implementing the allocation sequence: sequentially numbered: The allocation sequence will be implemented using sequentially numbered, sealed, opaque envelopes to ensure concealment until the point of assignment. |
| Implementation | 16c | Who will generate the allocation sequence: a statistician. who will enrol participants, and who will assign participants to interventions: principal investigator. |
| Blinding (masking) | 17a | Who will be blinded after assignment to interventions (eg, trial participants, care providers, outcome assessors, data analysts), and how: Opaque, sealed envelopes containing the assigned treatment group (coded as Group A or Group B) will be used. The principal investigator will maintain a record of patient names, randomization dates, and code numbers. However, the key linking the code to the actual treatment (ozone or oxygen) will be known only to the randomization investigators and Chronic Pain Unit staff, remaining hidden until the analysis is completed. |
|  | 17b | If blinded, circumstances under which unblinding is permissible, and procedure for revealing a participant’s allocated intervention during the trial: If unblinding is necessary, it will only be permitted in cases of medical emergencies where knowledge of the assigned intervention is essential for the participant's clinical management. In such cases, the principal investigator will unblind the treatment group. All unblinding events will be recorded and justified. |
| **Methods: Data collection, management, and analysis** | | |

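### Emergency unblinding is given to a principal investigator who is not a key holder, and with two shared codes one code-break can decode up to all 42 allocations for that role

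*Protocol*

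**What the plan says.** The relevant text is in items 16a, 16c, 17a and 17b of the Protocol.

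- **Coding (16a, 17a).** "Opaque, sealed envelopes containing the assigned treatment group (coded as Group A or Group B) will be used". No treatment code specific to a patient and no individual code-break envelope is described.
- **Record (16a, 17a).** "The principal investigator will maintain a record of patient names, randomization dates, and code numbers".
- **Key (16a, 17a).** The link from code to gas is "known only to the randomization investigators and Chronic Pain Unit staff, remaining hidden until the analysis is completed".
- **Assignment (16c).** The person named to enrol and to assign is the same: "who will enrol participants, and who will assign participants to interventions: principal investigator".
- **Emergency unblinding (17b).** It is allowed only in a medical emergency, and each event is to be recorded and justified. On who does it: "In such cases, the principal investigator will unblind the treatment group".

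Item 14 sets the sample at 42 patients, 21 per group. Item 21a has the principal investigator and the clinical research team review adverse events and adherence while the trial runs.

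**The concern.** Two things are wrong together. First, item 17b gives a task to someone who, under 16a and 17a, does not hold the means to do it. An emergency procedure should not leave open who can carry it out. Second, the code is shared across patients. A code-break is meant to expose one patient, but with only two letters it also exposes the meaning of the letter, and so the treatment of everyone whose letter is known.

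What is at stake is the masking of the principal investigator. That role reviews adverse events and adherence. Item 22 has the clinical research team judge whether events are related to the intervention, and treatment toxicity is a secondary outcome (item 12). A reviewer who knows all allocations could weigh events differently in the two arms without intending to.

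**Working it through.** The protocol states no figure on this point. The check sets the items side by side and then counts the allocations that one code-break discloses.

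**Step 1: do 16a/17a and 17b agree?**

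| Question | 16a and 17a | 17b |
|---|---|---|
| Who can translate A/B into ozone or oxygen? | Randomisation investigators and Chronic Pain Unit staff only | The principal investigator unblinds; no key-holder step is given |
| When? | Not before the analysis is completed | During the trial, in an emergency |

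Either the principal investigator has access to the key, and 16a/17a are wrong, or the principal investigator must get the answer from a key holder, and 17b leaves out that step. The text does not settle which.

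**Step 2: does the principal investigator know patients' letters?** The protocol does not say so outright. It follows from 16c: the principal investigator assigns patients, and what the envelopes contain is the group letter. The record of code numbers points the same way, because the next sentence in 16a and 17a contrasts that record with the key that decodes it. If those code numbers are only study identification numbers (item 27 mentions a unique study code), the inference from 16c still stands.

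**Step 3: what does one code-break disclose?** Inputs: N = 42 patients (item 14) and two codes for two treatments (16a).

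- Shared codes: if a patient with letter A is found to have received ozone, then A = ozone and B = oxygen. If the patient received oxygen, the reverse holds. Either way both letters are decoded.
- Suppose k patients have been assigned at the time of the event. The treatment of those k is then readable by anyone who knows their letters. The other 42 − k become readable as each is assigned. The ceiling is k + (42 − k) = 42 of 42.
- Patient-specific codes: one break gives 1 of 42, and 1/42 = 0.024, or 2.4%.

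**Step 4: who is affected?** The principal investigator, and anyone else who knows the letters. Nothing in the text passes the information on to patients or outcome assessors.

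**The case against.** The strongest reply is that 17a describes the normal state and 17b a narrow exception. On that reading the principal investigator only authorises disclosure and a key holder supplies it, for one participant, with the event recorded. This is a reasonable guess at the intent, but 17b does not say it. Even if it did, the shared letter would defeat a disclosure meant for one patient.

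The reply is also right that 42 of 42 is a ceiling. It needs an emergency unblinding to happen, and the protocol gives no basis for a probability. It also needs the principal investigator to know the letters, which is inferred from 16c.

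A reader might go further in four ways that the document does not support:

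- **Loss of blinding for the whole trial.** One role would be unblinded. Both primary outcomes are self-reported, patients would stay masked, and the protocol does not say that the principal investigator assesses outcomes.
- **Biased enrolment.** Item 16b uses sealed, opaque envelopes numbered in sequence. Knowing that A means ozone does not show which letter comes next.
- **A false claim of care-provider masking.** Item 7 says "Masking will be triple: participant, care provider, and outcomes assessor", but 16a specifies that the care providers meant are the oncologists and haematologists. It also states openly that the key "will be known only to the randomization investigators and Chronic Pain Unit staff". An unblinded operator who sets the gas is ordinary and is disclosed.
- **Disclosure through the interim look.** Item 21b does not say that results will be shown by group letter.

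**Conclusion.** The point holds as a contradiction between 16a/17a and 17b, joined to a coding scheme that cannot confine a code-break to one patient. If an emergency unblinding occurs, up to 42 of 42 allocations become readable to the principal investigator and to others who know the letters, where patient-specific codes would expose 1 of 42.

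This rests on two assumptions: that an emergency unblinding takes place, and that assigning from the A/B envelopes shows the principal investigator the letters. The consequence is limited to the masking of a role that reviews safety and adherence. Patients, outcome assessors and the concealment of the next envelope are not compromised by this route alone. The amendment is worth making because the change is small and the contradiction has to be resolved in any case.

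**What to change.** **Items 16a and 17a.** Replace the two group letters with a unique treatment code for each patient, or keep an individual code-break envelope per patient. The envelope used at assignment should then carry only the patient-specific code. The list linking codes to gas stays with the existing key holders.

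**Item 17b.** State that, on the principal investigator's request in a medical emergency, a key holder reveals the allocation of that patient only, and that the event is recorded and justified as now. This brings 17b into line with 16a and 17a.

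**Cost.** A new code list, new envelope labels and a short amendment, using roles that already exist. The protocol does not give enrolment status. If enrolment has begun, recoding can apply only to patients not yet assigned; for those already assigned, a key holder should do the single-patient code-break. Some exposure would remain: a break in a patient who already carries a letter could still decode the others assigned by letter, but not those with patient-specific codes.

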| Participant timeline | 13 | Time schedule of enrolment, interventions (including any run-ins and washouts), assessments, and visits for participants. A schematic diagram is highly recommended (see Figure 1) |
| Sample size | 14 | The sample size of 42 patients (21 per group) was calculated using GRANMO software (<https://www.datarus.eu/aplicaciones/granmo/>). This is based on an expected clinically relevant reduction in symptoms (>50% decrease in numbness and tingling from baseline) in at least 50% of the ozone group patients, compared to less than 10% in the placebo group, with 80% power, a one-sided alpha of 0.05, a 1:1 ratio, and accounting for 10% possible loss to follow-up. |
| Recruitment | 15 | Strategies for achieving adequate participant enrolment to reach the target sample size in a clinical trial: Engaging referring clinicians: Collaborate with oncologists, general practitioners, or other relevant specialists to identify and refer eligible patients. Patient outreach and education: Use flyers, informational sessions, social media, or community events to raise awareness about the study and its potential benefits. Providing clear informed consent materials: Ensure patients fully understand the study, its procedures, and potential benefits/risks, to increase willingness to participate. Leveraging patient registries or databases: Use hospital records, disease registries, or electronic medical records to identify potential participants systematically. Monitoring recruitment progress regularly: Track enrolment metrics weekly or monthly to identify bottlenecks early and adjust strategies as needed. |
| **Methods: Assignment of interventions (for controlled trials)** | | |
| Allocation: |  |  |

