| Data management | 19 | Plans for data entry, coding, security, and storage, including any related processes to promote data quality (eg, double data entry; range checks for data values). Reference to where details of data management procedures can be found, if not in the protocol:  Data will be entered into a secure, password-protected electronic database by trained personnel. To ensure data quality, the study will implement double data entry for critical variables and perform regular range and consistency checks to identify and correct discrepancies. All data will be coded using standardized coding systems, and personal identifiers will be removed or anonymized to protect participant confidentiality.  Access to the database will be restricted to authorized study staff only. Regular backups will be conducted, and data will be stored on encrypted servers in compliance with institutional and regulatory requirements.  If not fully detailed in the study protocol, additional information on data management procedures will be available in the study’s Data Management Plan (DMP), which can be provided upon request. |
| Statistical methods | 20a | Statistical methods for analysing primary and secondary outcomes. Reference to where other details of the statistical analysis plan can be found, if not in the protocol:  A double analysis will be performed: "by intention to treat" (all included patients) and "by protocol" (only patients who completed the study in their assigned group). Normality will be assessed using the Kolmogorov-Smirnov test. Depending on data distribution, parametric or non-parametric tests will be used for comparisons between groups. Contingency tables will use the chi-square test. Variables with more than two follow-up assessments will be analysed using a mixed generalized linear model with repeated measures. Bonferroni adjustment will be applied for multiple comparisons, with a p-value < 0.05 considered significant. |
|  | 20b | Methods for any additional analyses (eg, subgroup and adjusted analyses): non applicable. |

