|  | 20c | Definition of analysis population relating to protocol non-adherence (eg, as randomised analysis), and any statistical methods to handle missing data (eg, multiple imputation): The primary analysis will follow the intention-to-treat (ITT) principle, including all participants as randomized, regardless of protocol adherence. This approach preserves the benefits of randomization and provides an unbiased estimate of treatment effect.  For participants who deviate from the protocol or discontinue the intervention, all available outcome data will be included in the analysis. To handle missing data, we will use appropriate statistical methods such as multiple imputation, assuming data are missing at random. Sensitivity analyses may also be conducted to assess the impact of different missing data assumptions on the results. |
| **Methods: Monitoring** | | |
| Data monitoring | 21a | Composition of data monitoring committee (DMC); summary of its role and reporting structure; statement of whether it is independent from the sponsor and competing interests; and reference to where further details about its charter can be found, if not in the protocol. Alternatively, an explanation of why a DMC is not needed.  A Data Monitoring Committee (DMC) is not deemed necessary for this study due to its relatively low-risk nature, the non-invasive intervention (rectal ozone therapy), and the short to moderate duration of participant involvement. The study does not involve high-risk treatments or vulnerable populations, and the expected adverse events are minimal and well-characterized based on prior clinical experience.  Safety will be monitored internally by the principal investigator and the clinical research team, who will review adverse events and protocol adherence on an ongoing basis. In case of any serious or unexpected adverse events, these will be reported immediately to the ethics committee and relevant regulatory authorities, as per standard procedures.  Given these factors, the establishment of an independent DMC is not required. Full details of the safety monitoring procedures are included in the study protocol. |

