|  | 21b | Description of any interim analyses and stopping guidelines, including who will have access to these interim results and make the final decision to terminate the trial:  An interim safety analysis will be conducted when patient #21 completes follow-up, with the possibility of premature study termination if unforeseen serious complications or differences are statistically and clinically relevant in the main clinical outcomes after evaluation by the Ethics Committee  Safety and participant well-being will be continuously monitored by the principal investigator and the clinical research team. In the event of unexpected adverse events or safety concerns, the research team will review the data and, if necessary, consult the ethics committee to determine whether the trial should be modified or terminated. Access to any such safety data will be restricted to the research team responsible for monitoring adverse events. |
| Harms | 22 | Plans for collecting, assessing, reporting, and managing solicited and spontaneously reported adverse events and other unintended effects of trial interventions or trial conduct: All adverse events (AEs), whether solicited or spontaneously reported, will be systematically collected throughout the study period. Participants will be asked about any symptoms or changes in health during each scheduled visit, and any reported AEs will be documented in the case report forms (CRFs).  Each AE will be assessed by the clinical research team in terms of severity, duration, and relationship to the study intervention. Serious adverse events (SAEs) will be reported immediately to the ethics committee and relevant regulatory authorities, in accordance with applicable guidelines.  All AEs and SAEs will be managed according to standard clinical practice. Appropriate medical care will be provided as needed, and participants will be followed until the resolution or stabilization of the event. The principal investigator will be responsible for ensuring that all safety information is reviewed regularly and that appropriate action is taken if safety concerns arise. |

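### The look at patient 21 is labelled a safety analysis but may end the trial on significant main-outcome differences with no boundary; 0.05 at both looks gives about 8% type I error

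*Protocol*

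**What the plan says.** Item 21b (interim analyses and stopping guidelines) schedules one interim analysis, described as a safety analysis, when the 21st patient completes follow-up. It gives two grounds for ending the trial, subject to Ethics Committee evaluation: the "possibility of premature study termination if unforeseen serious complications or differences are statistically and clinically relevant in the main clinical outcomes". It states no direction for the differences, no significance level and no boundary.

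The only significance threshold for analyses is in item 20a: "Bonferroni adjustment will be applied for multiple comparisons, with a p-value < 0.05 considered significant". That sentence does not mention the interim look. Item 14 sizes the trial at 42 (21 per group) "with 80% power, a one-sided alpha of 0.05, a 1:1 ratio, and accounting for 10% possible loss to follow-up", and does not mention it either. Items 7 and 12 name two primary outcomes at week 28: self-perceived numbness/tingling and EQ-5D-5L.

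Item 21a dispenses with a data monitoring committee: "Safety will be monitored internally by the principal investigator and the clinical research team". Items 16a and 17a code the arms A and B. The key is known to the randomization investigators and Chronic Pain Unit staff, "remaining hidden until the analysis is completed". Item 21b restricts access to safety data to those monitoring adverse events, but names nobody for interim efficacy results.

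**The concern.** The label and the rule disagree. A review limited to harms costs no efficacy alpha. A rule that may end the trial because the main outcomes differ significantly is a second chance to declare an effect, and it needs a boundary or a reduced final level. Item 21b is where stopping guidelines belong, and it states a criterion. So this is a rule that is unsound as written, and not just a detail left to a later analysis plan.

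Three things are at stake:
- **Error rate.** It is no longer the 5% on which the sample size rests.
- **Effect estimate.** A trial stopped for a significant difference at about 10 patients per arm reports too large an effect.
- **Masking.** Acting on a difference requires knowing its direction, and the protocol does not reconcile this with keeping the treatment key hidden.

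**Working it through.** **Inputs.** N = 42, 21 per group; 50% v 10% responders; one-sided alpha 0.05; 80% power; 10% loss (item 14). Threshold p < 0.05 (item 20a). Interim at patient 21 (item 21b), so the information fraction is t = 21/42 = 0.5. Two primary outcomes (item 7). *Assumption:* 0.05 is also the interim threshold, because no other is stated.

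**1. The plan's sample size.** With d = 0.4 and mean rate 0.3, the one-sided formula gives n = [1.645·√(2·0.3·0.7) + 0.842·√(0.25 + 0.09)]² / 0.16 = 15.15 per arm. The continuity correction n/4·[1 + √(1 + 4/(n·d))]² raises this to 19.83. Multiplying by 1.1 gives 21.8, so 22 per arm and 44 in total, within two patients of 42. The two-sided arcsine formula gives 18.26/0.9 = 20.3, so 21 per arm and exactly 42. None of these formulas contains a term for an interim look, so item 14 uses the whole 0.05 once.

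**2. One outcome, two looks.** The interim and final statistics are correlated √0.5 = 0.707.
- Two-sided: 1 − P(|Z₁| ≤ 1.96, |Z₂| ≤ 1.96) = **8.3%** (8.6% to 8.0% for t = 0.4 to 0.6).
- One-sided: 1 − P(Z₁ ≤ 1.645, Z₂ ≤ 1.645) = **8.0%** (8.3% to 7.7%).

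**3. Responder comparison.** Exact binomial enumeration of the uncorrected chi-square test, 11 v 10 at the interim and 21 v 21 at the end, with the same rate in both arms:

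| Common rate | Two-sided: final only → both looks | One-sided: final only → both looks |
|---|---|---|
| 10% (item 14's placebo ceiling) | 4.1% → 6.0% | 5.3% → 7.0% |
| 20% (assumption) | 5.2% → 9.2% | 5.2% → 8.7% |
| 30% (assumption) | 5.6% → 9.9% | 5.4% → 8.4% |

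**4. Two primary outcomes with Bonferroni 0.025 each at both looks.** Per outcome the two-look error is 4.28%. For independent outcomes, 1 − (1 − 0.0428)² = 8.4%. Simulation with an assumed correlation of 0.7 gives 7.3%.

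**5. Effect estimate after a stop.** At the protocol's own 50% v 10%, exact enumeration of interim results significant at two-sided 0.05 gives a mean observed difference of about 51 points (10 ozone, 11 placebo) to 53 points (11 and 10). The true difference is 40.

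**6. Boundaries that hold the level at t = 0.5.** Haybittle-Peto (interim two-sided p < 0.001, final 0.05) gives 5.0% for one outcome. With a final 0.025 for each of two outcomes it gives 2.54% per outcome, so at most 1 − (1 − 0.0254)² = 5.0% if they are independent, and less if they are positively correlated. Two-sided O'Brien-Fleming uses 0.0052 and then 0.0480.

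**The case against.** The strongest reply is that item 21b is not an automatic stop at p < 0.05. Termination is only a possibility, the difference must be clinically as well as statistically relevant, and the Ethics Committee evaluates first. An interim level of 0.05 is an inference, and a separate analysis plan might give a boundary.

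All of that stands as a limit on the size of the problem. The figures above are conditional, and a reader who infers a mechanical rule goes beyond the text. It does not rescue the rule, since neither brake is quantified. For the responder outcome, the smallest significant interim difference is already 3/11 v 0/10 = 27 points one-sided, or 4/11 v 0/10 = 36 points two-sided. A clinical-relevance condition would therefore remove little.

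The placebo rate may also be low, since item 14 expects "compared to less than 10% in the placebo group". At 5% the two-look two-sided error of the responder test is only 1.8%, because the test is then very conservative. That helps only a responder analysis. Item 12 defines the primary outcomes as changes on a percentage scale and on EQ-5D-5L, for which the roughly 8% figure is the relevant one.

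Bonferroni could be read as covering the two looks. At 0.025 per look, one outcome would be held at 4.2% to 4.3%. Item 20a does not say so, and the same 0.025 cannot also cover two primary outcomes.

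Finally, the clause could be meant for harm only, in which case no efficacy alpha would be spent. The text gives no direction, and serious complications are listed as a separate ground.

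**Conclusion.** The rule is wrong as written and should be changed before the interim look. If 0.05 is applied at both looks and stopping for benefit is possible, type I error is about 8% for one outcome. For the responder test it is 6.0% two-sided or 7.0% one-sided at a 10% common rate, and about 9% to 10% two-sided if that rate were 20% to 30%. With two primary outcomes under Bonferroni it is 7.3% to 8.4%. Clinical-relevance and Ethics Committee review could lower these figures by an unknown amount.

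Two stronger readings are not supported:
- **An error rate of 15% to 16%.** A reader might reach this by testing both primary outcomes at an undivided 0.05 at each look. That sets aside the Bonferroni sentence in item 20a.
- **Efficacy results reaching the recruiting team.** A reader might infer this because the principal investigator enrols and assigns patients (item 16c) and also leads safety review (item 21a). No section says who sees interim efficacy results, and the arms are coded A and B. The documented defect is that access is unassigned and there is no independent committee. A leak is not documented.

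**What to change.** **Preferred:** limit item 21b to safety. Delete the clause on differences in the main clinical outcomes and state that no between-arm test for benefit is done at patient 21. Efficacy alpha then stays at its planned level.

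**If an efficacy stop is wanted:** state a Haybittle-Peto rule in item 21b, with interim two-sided p < 0.001 per outcome. The final test stays at its planned level: 0.05 for one outcome, or Bonferroni 0.025 for each of two primary outcomes, about 5% overall. State that the comparison is run by a statistician outside the recruiting team, such as the independent randomization statistician in item 16a, and who may see the result.

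**Cost:** a short amendment to item 21b and no extra patients. The trial gives up the option to stop for benefit at a nominal p < 0.05. Because the present clause has no direction, deleting it outright also removes the formal between-arm comparison that could show worsening in the main outcomes on ozone. If that protection is wanted, keep the review explicitly as a safety item.
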